**Method:**

In a two-armed, randomised controlled study design adolescents and young adults from 14 years old will be recruited. Following an initial baseline assessment, they will be randomised to a) the intervention group (IG, *n* = 75), which will receive a mHealth intervention (the application ‘Mental Health Guide’, co-developed by lived experience experts) or b) the waiting list control group (CG, *n* = 75). Both groups will be followed up after 3 and 6 months following post assessment. We hypothesize an increase in mental health literacy in the IG compared to the CG for post and follow-up assessment (primary outcome: Mental Health Literacy Scale). In addition, we expect an improvement in mental health and psychological well-being, improved emotion regulation, reduced psychological distress, as well as good quality ratings in usability and acceptance in the use of the ‘Mental Health Guide’ We performed multiple simulations of possible outcome scenarios, incorporating an array of factors, to generate realistic datasets and obtain accurate estimates of statistical power.

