### Design

2.1

The study is a randomised controlled trial aiming to promote MHL and strengthen the mental health of *N* = 150 adolescents and young adults, as well as evaluating the usability and acceptance of the MHG. Fig. 1 provides an overview over the study design. In a parallel two-arm design, participants will be randomly assigned to the intervention group (IG, *n* = 75) or the waiting list control group (CG, n = 75) after a baseline online questionnaire by a computerised random generator, based on codes only. The IG will receive access to the MHG after a baseline measurement. The CG will receive access to the MHG after a post- and 3-month follow-up assessment. The relatively long waiting time of the CG until the intervention (6 months) is necessary as a comparison for the developments of the IG, but justifiable due to the preventive nature of the intervention. To capture and compare the ratings in usability and acceptance at the CG, further assessments will be administered at 6 months after the post-measurement. Additionally, to capture daily fluctuations in mood dynamics and emotion regulation, we carry out an ecological momentary assessment (EMA), to complement the pre-post-assessment with participants' experience in real-time (Schiffman et al., 2008).

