#### Control group

2.4.2

The control group does not receive an intervention between pre-measurement and 3-month follow-up. They will get access to the MHG between the 3-month and the 6-month follow-up.

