### Statistical analysis

2.6

The main analyses will be performed in *R* (R Core Team, 2022). A mixed-measures analysis of variance (ANOVA) will be conducted with time (four levels: baseline, post, first follow-up, second follow-up) as the within-subjects factor and group (two levels: experimental, control) as the between-subjects factor. The model will contain independent variables for *Group* (coded 0 = CG and 1 = IG), *Time* (coded *Time* = 0, 1, 2, 3) and an interaction effect *Group* x *Time*. This analysis allows investigation not only of the main effects of time and group but also the interaction effect between time and group, which is crucial in understanding if the changes over time differed significantly between the two groups. In cases where significant interactions or main effects are found, post hoc analyses will be conducted to identify specific differences between time points and groups. Additionally, multi-level models with random intercepts and polynomial time variables will be estimated to evaluate differential longitudinal changes and potential non-linear pattern over time in the primary outcome (MHLS) across subjects in the treatment and control group (Hilbert et al., 2019).

In further exploratory analyses, the treatment effect will be investigated for the secondary outcomes in a similar fashion, and the moderating effect of app usage and acceptance on the treatment effects will be considered. Additionally, from the EMA data, properties of mood dynamics and emotion regulation competencies during everyday life will be derived using time-series analysis (e.g., autoregressive models and spectral analysis) and evaluated in their predictive capability for outcome measures (Schubert et al., 2021; Seizer et al., 2022).

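### The main Group x Time test includes a 6-month wave measured after the control group has had the app, so it mixes app versus no app with early versus delayed access

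*Protocol article*

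**What the plan says.** Section 2.6 (Statistical analysis) sets up the main model as a mixed ANOVA with "time (four levels: baseline, post, first follow-up, second follow-up) as the within-subjects factor". Group is a fixed 0/1 code, and time is described as "coded *Time* = 0, 1, 2, 3". The Group x Time interaction is singled out as the term "which is crucial in understanding if the changes over time differed significantly between the two groups". Comparisons at single time points come second: "In cases where significant interactions or main effects are found, post hoc analyses will be conducted". Multi-level models with polynomial time are planned in addition.

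On timing, Section 2.1 (Design) states: "The CG will receive access to the MHG after a post- and 3-month follow-up assessment". Section 2.4.2 (Control group) agrees: "They will get access to the MHG between the 3-month and the 6-month follow-up". Table 2 schedules the primary outcome, the Mental Health Literacy Scale (MHLS), at all four waves. Section 2.1 presents the control group's wait as the basis for comparison with the intervention group. It ties the 6-month assessment to usability and acceptance ratings in the control group.

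The abstract states the hypothesis as "We hypothesize an increase in mental health literacy in the IG compared to the CG for post and follow-up assessment", without saying which follow-up is meant.

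**The concern.** The period with an untreated comparator ends at the 3-month follow-up, but the main model runs one wave past it. Nothing in the model marks the control group's change of status. Two consequences follow, depending on how time enters.

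- **Time as a factor.** The interaction pools information from before and after the control group's access. A significant result could come partly from the control group improving once it has the app.
- **Time as the number 0 to 3.** The interaction is a difference in straight-line slopes. If both arms respond to the app, the last wave pulls that slope towards zero, and a real effect at post and 3 months could be missed.

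Section 2.6 can be read either way: it calls time a four-level factor and then gives it a numeric code.

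**Working it through.** **Inputs from the protocol.** N = 150, 75 per arm (2.1). Pooled d = 0.62, about 20% missing data, alpha 5%, power over 80% (2.6). With 20% missing, 150 x 0.8 = 120, or n = 60 per arm.

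**Assumptions not in the protocol.** Equal within-person correlation rho between waves (0.5, with 0.3 and 0.7 as a range); two-sided tests; the full effect d at both post and 3 months; and the amount by which the control group catches up by 6 months.

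**The protocol's own power statement.** With f = d/2 = 0.31, a four-wave interaction F test has noncentrality 120 x 0.31² = 11.53 on 3 and 354 df. Power is 0.819, which agrees with the stated figure. The power code is not shown, so this is a reconstruction, not proof of the method used.

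**Expected differences, intervention minus control, over the four waves.**
- No catch-up: (0, d, d, d)
- Half catch-up: (0, d, d, d/2)
- Full catch-up: (0, d, d, 0)

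**Formulas.**
- 3-df interaction: lambda = (n/2) x SS/(1 − rho), where SS is the sum of squared deviations of the differences from their mean. SS is 0.75d², 0.6875d² and d², so at rho = 0.5 lambda is 17.3, 15.9 and 23.1.
- Linear interaction: weights −1.5, −0.5, 0.5, 1.5, divided by 5. With no catch-up the slope is (−0.5d + 0.5d + 1.5d)/5 = 0.3d = 0.186. With half it is 0.15d = 0.093. With full it is (−0.5d + 0.5d)/5 = 0. The standard error is √[(2/60)(0.5)/5] = 0.0577.
- Group main effect: the mean of the four differences, 0.75d, 0.625d or 0.5d. The standard error is √[(2/60)(1 + 3 x 0.5)/4] = 0.144.

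**Results at rho = 0.5.**

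| Control catch-up | 3-df power | Linear slope (SD per wave) | Linear power | Mean difference (SD) | Main-effect power |
|---|---|---|---|---|---|
| None | 0.95 | 0.186 | 0.90 | 0.465 | 0.89 |
| Half | 0.93 | 0.093 | 0.36 | 0.388 | 0.76 |
| Full | 0.99 | 0 | 0.05 | 0.310 | 0.57 |

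For none, half and full catch-up, linear power is 0.78, 0.27 and 0.05 at rho = 0.3, and 0.99, 0.55 and 0.05 at rho = 0.7. The 3-df test has 0.85, 0.81 and 0.94 at rho = 0.3, and at least 0.995 throughout at rho = 0.7. Its lambda is largest under full catch-up: the control group's own response adds to the signal.

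**Contrast at 6 months alone.** Power is 0.92 with no catch-up, 0.39 with half and 0.05 with full.

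**Polynomial models.** The quadratic weights (1, −1, −1, 1) give −2d under full and −1.5d under half catch-up, with standard error √[(2/60)(0.5)(4)] = 0.258. Power is above 0.99 and about 0.95.

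**Three waves only.** For (0, d, d), SS = (2/3)d² and lambda = 15.4 at rho = 0.5. Power of the 2-df interaction is 0.85, 0.95 and 0.997 at rho 0.3, 0.5 and 0.7. If the effect halved by 3 months, (0, d, d/2), it would be 0.73, 0.87 and 0.98.

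**The case against.** A reader might infer that the 6-month wave cancels a true effect in the main test. The protocol does not support that as a general statement. A within-subjects factor with four levels is most naturally categorical, and the 0 to 3 code may be no more than level labels. On that reading the 3-df test loses almost nothing. Complete cancellation needs numeric time, full catch-up and a stable intervention group all at once. App use is at the participants' discretion (2.3, 2.4.1), so nothing in the document supports full catch-up in particular.

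A reader might also infer that the p-value says nothing about whether the app works. That too goes too far. If the app has no effect, giving it to the control group changes nothing, all expected differences are zero, and the factor test is valid. Early against delayed access is also what was randomised. What is lost is the attribution of a significant result to the period with an untreated comparator.

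The planned polynomial models could detect the curved pattern, and post hoc tests could isolate post and 3 months. Both points stand, with limits. The polynomial models are additional and keep the same group label, so their curvature also contains the control group's response. The post hoc tests depend on a significant omnibus result.

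Finally, the hypothesis does not name 6 months. Superiority at that wave is one possible reading of its wording, not an explicit claim.

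**Conclusion.** The point holds in a limited form. Sections 2.1, 2.4.2 and 2.6 and Table 2 together show that the main model does not separate the comparison with an untreated group from the wave after the control group's access, and that the role of time is ambiguous.

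Under the factor reading the harm is to interpretation, not to power or type I error. Under the numeric reading there is a real loss of power, from 0.90 to 0.36 at half catch-up and to 0.05 at full catch-up (rho = 0.5). The group main effect is diluted under either reading, from 0.465 SD to as low as 0.31 SD under full catch-up, although the protocol treats the interaction as the key term. These sizes rest on assumed correlations, an assumed amount of catch-up, 60 analysed per arm and a sustained d = 0.62. That the last wave lacks an untreated comparator rests on none of them. Should be fixed.

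**What to change.** 1. State that time is categorical in the main model, and remove the numeric code or label it as level names only.
2. Base the confirmatory test on baseline, post and 3-month follow-up. Alternatively, keep four waves and prespecify the Group x Time contrasts at post and 3 months as the confirmatory test, not conditional on the omnibus result.
3. Report the 6-month wave separately as early versus delayed access: maintenance in the intervention group, and change from 3 to 6 months in the control group, labelled as uncontrolled. Interpret polynomial models that include this wave in the same way.
4. State that the superiority hypothesis for follow-up refers to the 3-month follow-up.

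The cost is wording in the analysis section and a clarification of the hypothesis. No data are lost, the 6-month assessment stays, and power remains above 80% on the protocol's own effect size across the correlations examined, provided the effect lasts to 3 months. The Trial status section says analysis has not begun, so the change can be recorded before it does.

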### Procedure

2.3

School classes are informed about the study and the conditions of participation by the study staff. Interested students can provide consent directly via a QR code. Interested students under the age of 18 need to forward an information letter to their parents for the initial parental consent to the study. For participants over the age of 18 who are recruited via social media, all study information will be provided, and consent will be given online. The consent form of participants is automatically followed by the digital baseline survey. In addition, participants will be prompted for the EMA survey via smartphone twice a day (at 7 am and 9 pm) for one week as part of each assessment. After the baseline questionnaire (before the EMA survey), participants receive information whether they were randomised to either the IG or CG. As soon as the EMA survey is finished, the IG will receive access to the MHG. The IG may use the MHG at their discretion and will not be prompted to use it during the 12 weeks of use.

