#### MHG

2.4.1

The MHG is a self-help e-learning course developed and distributed by a social company called the Mental Health Crowd. The app was developed amongst others by experts with lived experience of mental illness, psychologists, coaches and therapists. The motivation behind the co-development with lived experience experts and decisive for the selection of modules was to bring personal experiences into the designs in order to make the app more user-oriented. The study team was not and is not involved in the development or distribution of the app. The MHG can be used as a progressive web application on a smartphone, or as a desktop version via an Internet browser. In 12 modules, participants learn which factors influence mental health and how they can influence it. There is no predefined order in which modules should be worked through and by when to increase flexibility and address individual interests (see an overview of all modules displayed in Table 1 and in detail in supplemental 1). Users are informed that they should work independently on the topic that interests them most from an overview of the 12 modules. They are not given any specific recommendations. The content is presented to the user in a mixture of videos, texts, images, impulses, and quizzes. Personal counseling is not offered within the MHG due to limited resources. The processing period of the individual modules amounts to a suggested time of 12 weeks, so that each module can be sufficiently processed within one week. The processing period of a single module with its subsection varies between 20 and 60 min. However, when and for how long participants actually use the MHG is up to them personally and is not controlled or requested.

**Table 1 t0005:** Summary of the 12 MHG modules.

Module	Content
#1 – Body	Healthy nutrition, exercise, sleep, breathing, stimulants
#2 – Stress and resources	(Physical) effects of stress, handling stress
#3 – Here and now	Mindfulness, change in life
#4 – Circumstances	Finances and consumer goods, geographical and temporal circumstances, human, mindset
#5 – Emotional intelligence	Fundamental information of emotions, emotions in myself and others
#6 – Needs	Fundamental information of human needs, communication of needs
#7 – Relationships with others	Roles in everyday life, social skills, forgiving
#8 – Relationship with me	Self-care, beliefs
#9 – Crisis	Dealing with crises, exercise for coping strategies

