Power analyses were performed in R 4.2 (R Core Team, 2022) using functionalities of the package *WebPower* (Zhang and Yuan, 2018). A previous meta-analysis that summarized results on the effectiveness of mental health literacy interventions in young people found moderate effect sizes (pooled *d* = 0.62) and average retention rates of about 86 % (Mills et al., 2023). Assuming the pooled effect size of previous interventions and a missing data rate of about 20 %, the study will allow performance of the planned analyses at a statistical power of over 80 % and an alpha error of 5 %. Full reproducible code and further information for the power analyses are available in the supplementary material and on OSF (https://osf.io/4wh5x/?view_only=040375cd3a56472597e788b97e5b8f28).

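### The supplementary multi-level model for the MHLS names random intercepts but no random slope or serial correlation, so its linear Group x Time test can exceed the stated 5 % error by an amount that depends on quantities not given

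*Protocol article*

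**What the plan says.** Section 2.6 (Statistical analysis) lists first a mixed ANOVA of group and "time (four levels: baseline, post, first follow-up, second follow-up) as the within-subjects factor", and treats its interaction as the key result. As an addition for the MHLS, it then states that "multi-level models with random intercepts and polynomial time variables will be estimated to evaluate differential longitudinal changes" and possible non-linear patterns in the two arms. Time is coded 0, 1, 2, 3. No random slope, residual correlation or robust standard error is named, nor is the polynomial Group x Time term that will be tested. Secondary outcomes are to be handled similarly.

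The same section claims for the planned analyses a "statistical power of over 80 % and an alpha error of 5" %. Section 2.3 (Procedure) says of the app: "The IG may use the MHG at their discretion and will not be prompted to use it during the 12 weeks of use". Section 2.4.1 (MHG) adds that "when and for how long participants actually use the MHG is up to them personally and is not controlled or requested".

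**The concern.** A model whose only random effect is the intercept lets participants start at different levels but makes everyone in an arm follow the same curve from there. It also implies the same correlation between baseline and post as between baseline and the last follow-up, about nine months later (12 weeks of use plus six months). That sits poorly with a model intended to study differences in change.

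The consequence concerns inference, not bias. Person-to-person variation in change, or correlation that weakens with distance in time, is spread over all the within-person residuals as if it were independent noise. The linear contrast carries more than its share of that variation, so its standard error is understated. At stake is that a chance difference in slope between the arms on the primary outcome is reported as an app effect, with an interval that is too narrow.

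**Working it through.** **Inputs from the article.** Allocation: "intervention group (IG, *n* = 75) or the waiting list control group (CG, n = 75"). Effect: "found moderate effect sizes (pooled *d* = 0.62"). Missing data: "a missing data rate of about 20" %, which leaves 150 x 0.8 = 120, or 60 per arm. Four waves coded 0 to 3. Alpha 5 %; sidedness is not stated and two-sided is assumed. Cronbach's alpha of the MHLS is 0.873 (section 2.5.1).

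**Not in the article, so assumed and varied.** Slope variance, residual variance and serial correlation of the MHLS.

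**1. The plan's own figure.** With f = d/2 = 0.31 and n = 120, the noncentrality is 0.31² x 120 = 11.53. The 3 df interaction (error df 118 x 3 = 354) has power 81.9 %. A two-group comparison with 60 per arm has 92.4 %. The claim of over 80 % reproduces and is not in question.

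**2. Slopes that vary between people.** Let x = slope variance / residual variance. For times 0 to 3 the within-person sum of squares is 5. In units of the residual variance, the linear contrast has true variance 1 + 5x. The random-intercept model instead uses the average over the three within-person contrasts, (1 + 5x + 1 + 1)/3 = 1 + 5x/3. Hence

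ratio = (1 + 5x)/(1 + 5x/3), and actual alpha = 2[1 - Phi(1.96/√ratio)].

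Worked case, slope SD 0.4 of residual SD: x = 0.16, ratio = 1.80/1.267 = 1.421, 1.96/1.192 = 1.644, alpha = 10.0 %.

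The table assumes equal slope variation in both arms. The joint tests refer [(1 + 5x)Z1² + Z2²]/(1 + 5x/3), with Z3² added for 3 df, to the chi-square limits.

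| Slope SD / residual SD | Linear, 1 df | Linear + quadratic, 2 df | All three, 3 df |
|---|---|---|---|
| 0 | 5.0 % | 5.0 % | 5.0 % |
| 0.2 | 6.5 % | – | – |
| 0.25 | 7.2 % | 5.8 % | 5.1 % |
| 0.4 | 10.0 % | 6.9 % | 5.4 % |
| 0.5 | 12.0 % | 7.8 % | 5.7 % |
| 1.0 | 19.1 % | 11.6 % | 7.8 % |

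The quadratic term tested alone becomes conservative (2.7 % at 0.4). The 3 df column also describes the ANOVA interaction without a sphericity correction.

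**3. Check with dropout.** A REML random-intercept fit with 75 per arm, 20 % monotone dropout and 1,500 replicates per setting rejected a true null for the linear term in 4.5 % (ratio 0), 6.9 % (0.25), 10.3 % (0.4) and 12.3 % (0.5). This agrees with the formula.

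**4. Correlation that decays, with no random slopes.** Under AR(1) with parameter φ, the linear contrast has true variance 5[1 + (5φ - 6φ² - 9φ³)/10]. The model uses 5[1 - (3φ + 2φ² + φ³)/6].

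- φ = 0.8: 2.776/1.507 = 1.84, alpha = 14.9 %.
- φ = 0.6: 4.448/2.720 = 1.64, alpha = 12.5 %.
- Adding measurement error of 1 - 0.873 = 12.7 % of the variance: 11.0 % to 11.8 %.
- Adding also a stable trait (40 % of the variance): 10.1 % to 10.4 %.

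**The case against.** The strongest reply has five parts.

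- *The model is secondary.* This stands. The mixed ANOVA comes first, and its 3 df interaction is only modestly affected by slope variation (5.4 % at ratio 0.4). A reader might infer that the trial's main test is invalid; the article does not support that.
- *The size is not fixed by the article.* This stands. A reader might conclude that the test rejects about twice as often as stated. That is one point, a slope SD near 0.4 of the residual SD with the 1 df linear term, and nothing in the article selects it. The tested term is not named either, and joint tests inflate less.
- *Self-directed use does not prove the scenario.* This stands in part. If the app does nothing for anyone, varying use cannot create varying slopes, and before the 3-month follow-up only the intervention arm has access. With slope variation in that arm alone, the ratio at 0.4 is (1 + 2.5 x 0.16)/(1 + 2.5 x 0.16/3) = 1.235, giving 7.8 % (joint tests 5.9 % and 5.2 %). Natural differences in change and fading correlation do not depend on the app, but the article gives no data on them.
- *An article condenses, and naming random intercepts need not exclude slopes.* This has some force. Yet the random-effects structure is stated rather than left open, and what is stated is the intercept.
- *Group differences in change can be estimated with fixed interactions.* This is true of the estimates. It does not rescue their standard errors.

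**Conclusion.** The point holds as a correctable weakness in a supplementary model of the primary outcome. As specified, the model assumes equal correlation between all waves and no individual departure from the arm's curve. If either fails, its linear Group x Time test is anti-conservative. Under the stated assumptions (two-sided test, normal errors, equally spaced time codes), the error is about 6.5 % to 12 % for slope SD 0.2 to 0.5 of residual SD in both arms, and about 10 % to 15 % for AR(1)-type correlation of 0.6 to 0.8, with the lower end applying when measurement error and a stable trait are included. With negligible slope variation and constant correlation it stays at 5 %. The article shows neither that the inflation will occur nor how large it will be; it shows that the stated model gives no protection against it.

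**What to change.** In section 2.6, specify for the multi-level model either a random intercept and a random slope for time with their covariance, or categorical time with an unstructured within-person covariance. State that participant-clustered robust standard errors will be used if that fit does not converge. Name the Group x Time term to be tested: linear, or joint over the polynomial terms. Apply the same wording to the secondary outcomes, which follow this approach.

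A correctly specified covariance brings the test back to about 5 %. The cost is a model term and a few sentences, slightly wider intervals, and an occasional convergence problem with four waves, which the fallback covers. No new data are needed. The article's trial status section says analysis had not begun, so on that account the change could still be prespecified.
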